### Blinding

Research assistants, blinded to study hypotheses and treatment allocation, conducted baseline assessments prior to randomisation. Players were also blinded to study hypotheses and treatment allocation. After baseline assessments and randomisation, 4 coaches were asked to attend coach education sessions (intervention) and 4 coaches served as controls; therefore, it was not possible to keep coaches blinded in this study. Lastly, a member of the research team who was blinded to participant (player and coach) allocation conducted all analyses.

### Randomisation

Coaches were randomly assigned to the site they were coaching by using simple randomisation; a computer-generated algorithm was used, ensuring an equal number of coaches at each site. Players, however, were not randomly allocated to a site; instead parental preference in site determined where the player would attend the basketball program, and this was predominantly based on location of the venue in relation to their residence.

Group randomisation for both players and coaches occurred following baseline assessments. Coaches were pair-matched using the average step counts their group of players accumulated during two training sessions during baseline assessments (i.e., the two coaches with the two highest group step count averages during the training sessions and the two coaches with the two lowest group step count averages during the training sessions were paired together). Coaches were pair-matched to ensure that similar coaches (in terms of the average group step counts accumulated by their players during the baseline training sessions) were randomised into each arm of the study. Given that increasing MVPA was our primary outcome and that pedometry has been shown to be an accurate indicator of MVPA [19], matching coaches via group step counts was appropriate. Using a computer-generated algorithm one coach from each pair was allocated into the intervention arm and the other into the control arm.

Players at each site were randomly assigned using simple randomisation to either the intervention or control arm through a computer-generated algorithm, ensuring equal groups. To avoid clustering effects associated with having the same coach in each session throughout the program; players were randomised into different training groups and coaches within their allocated arm for each training session period for the duration of the program. Figure 2 illustrates the randomisation procedure for each training session for one site.

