### Sample size and power calculation

On the basis of an α of 0.05 and 80% power to detect a significant differential change in MVPA between groups, using an effect size of *d* = 0.6, a minimum sample size of 36 female players for each group was needed (*N* = 72). Our effect size is consistent with the findings of a recent systematic review and meta-analysis of interventions designed to increase children and adolescents’ MVPA in a similar setting (physical education), *d* = 0.62 [18]. To protect against player attrition and preserve adequate statistical power, the sample size was inflated by 10%, thus a total sample of 80 female players was sought.

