### Statistical analysis

All variables will be checked for normality using the Shapiro-Wilk test. Independent samples *t-*tests or Mann–Whitney *U-*tests will then be conducted, as appropriate, to examine: (1) baseline differences between groups and (2) baseline differences between players who completed the study and those lost to follow-up. If variables significantly differ between groups, they will be appropriately adjusted in the main analyses.

Linear mixed models will be used to analyse the differential change between groups on all outcomes from baseline to follow-up, using baseline data as the covariate. Linear mixed models will be used because these models are robust enough to withstand the biases from missing data, and provide good control of Type I and Type II errors [50]. All analyses will be conducted using SPSS 21.0 (Chicago, IL, USA). The level of significance will be set at *p* < 0.05.

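### Players are randomised within site, but the rule for choosing covariates will almost never bring site into the model, so some precision goes unused

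*Protocol article*

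**What the plan says.** **Allocation (Protocol article, Randomisation).** Parents chose which of the two sites their daughter attended. Arms were then formed inside each site: "Players at each site were randomly assigned using simple randomisation to either the intervention or control arm", with group sizes kept equal. Coaches were ranked on the baseline step counts of their groups and paired: "Using a computer-generated algorithm one coach from each pair was allocated into the intervention arm and the other into the control arm". The section gives similarity of coaches between arms as the reason for pairing. After allocation, players moved between coaches of their own arm from session to session.

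**Analysis (Statistical analysis).** All outcomes go into linear mixed models, "using baseline data as the covariate". The only stated route for another covariate is a test of baseline differences between arms (t-test or Mann–Whitney). Variables that differ significantly are then adjusted for. Site is not named.

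**Sample size (Sample size and power calculation).** The calculation is made "using an effect size of *d* = 0.6", and "a minimum sample size of 36 female players for each group was needed". It credits no gain from site, pairing or baseline.

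**The concern.** A factor used to restrict randomisation normally belongs in the analysis. Balancing arms within site removes site differences from the sampling error of the arm contrast. A model without site still counts those differences as residual noise, so its standard error describes a less precise trial than the one that was run.

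The covariate rule makes this systematic. It selects variables by imbalance between arms, and equal allocation within each site means that site has essentially no imbalance to find. Followed as written, the rule leaves out the one player-level design factor.

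A site effect is plausible. Parents chose the site mainly by distance from home, and each site had its own venue, coaches and data collection team (Study procedure). At stake are some power and a test that rejects less often than its nominal 5%. The estimate itself is not biased.

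**Working it through.** **1. The plan's own figure.** Inputs: d = 0.6, alpha 0.05, power 80%, with sidedness not stated ("On the basis of an α of 0.05 and 80% power").
- Formula: n per arm = 2(z_alpha + z_power)²/d².
- One-sided: 2(1.645 + 0.842)²/0.36 = 34.4, so 35, or 36 by the exact t calculation. This matches the plan.
- Two-sided: 2(1.960 + 0.842)²/0.36 = 43.6, so 44, or 45 by the exact t calculation.
- Attrition: 72/0.9 = 80, as stated.

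Sidedness is a separate matter. What counts here is that the planned 36 per arm relies on no gain from site.

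**2. Set-up for the site check.** There are 72 players, 36 per arm, with 18 per arm at each site. Total day-5 SD is 1 and d = 0.6. Assumed, because the documents do not give them: within-site correlation of day 1 with day 5, r = 0.5; site share of variance, s = 0.10 or 0.20; no coach effect; two-sided 5% test. For residual variance V, SE = sqrt(V(1/36 + 1/36)) = sqrt(V/18).

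**3. Model with site.** V = (1 − s)(1 − r²).
- s = 0.10: 0.90 × 0.75 = 0.675, SE 0.194.
- s = 0.20: 0.80 × 0.75 = 0.600, SE 0.183.

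**4. Model without site, site difference not carried by baseline.** The model's V becomes s + (1 − s)(1 − r²).
- s = 0.10: 0.775, estimated SE 0.207.
- s = 0.20: 0.800, estimated SE 0.211.

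The true SE of the estimate stays at 0.194 and 0.183, because the site difference cancels between balanced arms.

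**5. Model without site, the same site difference on both days.** The pooled slope is b = s + (1 − s)r, which is 0.55 or 0.60. The model's V is 1 − b², which is 0.6975 or 0.640, giving estimated SE 0.197 or 0.189. The true V is (1 − s)(1 − 2rb + b²):
- s = 0.10: 0.90 × 0.7525 = 0.677, true SE 0.194.
- s = 0.20: 0.80 × 0.76 = 0.608, true SE 0.184.

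**6. Power and type I error.** Simulation of the same set-up, 30,000 trials per row, analysed by ANCOVA with t tests:

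| Site share | Carried by baseline? | Type I error without / with site | Power without / with site | Gain (points) |
|---|---|---|---|---|
| 10% | no | 3.5% / 5.0% | 82.2% / 85.8% | about 4 |
| 20% | no | 2.4% / 5.0% | 82.6% / 89.5% | about 7 |
| 10% | yes | 4.8% / 5.2% | 84.8% / 85.5% | about 1 |
| 20% | yes | 4.3% / 4.8% | 88.4% / 89.8% | about 1 |

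With no site effect at all, power is 82.4% with or without the term, so the lost degree of freedom costs nothing visible.

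**The case against.** **The article is a summary.** A full analysis plan may list site. That would excuse silence, but the section is not silent. It states how covariates beyond baseline are chosen, and that rule works against a factor balanced by design. The point stands unless a fuller document overrides the rule.

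**The error is conservative, and baseline may absorb most of it.** Both parts are fair. The sample size claimed nothing from site, so omitting it does not take the trial below its planned power. Baseline activity was measured at the same site, and where it carries the site difference the gain is about 1 point. This keeps the point modest.

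**Stronger readings that a reader might infer, and that the documents do not support:**
- *Matching was built to gain precision, and the analysis throws this away.* The stated purpose of pairing is balance, and allocation achieves that.
- *The matched pair should be in the model as well.* Players rotate among coaches, so pair is not a player attribute. At coach level, four pairs leave 3 degrees of freedom against 6. In simulation with an effect of 2 coach SDs, the paired analysis had 49% power against 66% unpaired at zero pair correlation, and broke even near a correlation of 0.4. Several coach-level covariates on 8 coaches carry a similar cost.
- *Coach-level outcomes have no baseline adjustment.* The model uses baseline for all outcomes, so they do.
- *The SD shrinks by site's whole share of variance.* That ignores the baseline covariate. Only variance beyond baseline counts.

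**Conclusion.** The point holds for site in the player-level models. Randomisation is within site, and the stated covariate rule will almost never select site. The estimated standard error is then too large by an amount that depends on how much day-5 variance site explains beyond baseline. With r = 0.5 and a site share of 10–20%, both assumed, the power forgone runs from about 1 point to about 4–7 points. If site explains nothing beyond baseline, nothing is lost.

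The word conservative applies to this component alone. A reader might infer that the analysis as a whole is conservative, or that adding site would make it valid. Neither follows. If coaches differ and no coach term is fitted, the standard error is too small. With coach variance of 5, 10 or 20% of the total and no site effect, simulated two-sided type I error was about 11, 18 and 28%, and adding site left it essentially unchanged. That is a separate and more serious issue, which this change does not address.

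**What to change.** In Statistical analysis, state that every player-level model includes site (two levels) as a fixed effect alongside baseline, whatever the baseline comparisons show. Site should not be subject to the significance rule. For example: each player-level model will contain arm, the baseline value of the outcome and site.

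The cost is one degree of freedom. Each player's site is known from enrolment, so no new data are needed. The term should be fixed before the outcome data are analysed. No pair term and no added set of coach-level covariates is asked for under this point.

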## Methods/design

### Trial design

This study is a two-armed, parallel-group RCT, using a 1:1 allocation ratio, designed to investigate whether coaches who attended coach education sessions (where education on increasing MVPA and decreasing inactivity during training was delivered) can increase their players’ MVPA during training sessions over a 5-day basketball program; compared to coaches who did not receive coach education sessions (Figure 1). Outcomes were assessed at baseline (day 1 of the basketball program) and follow up (day 5 of the program). The Human Research Ethics Committee of the University of Western Sydney (UWS) approved this study. This study adheres to the Consolidated Standards of Reporting Trials guidelines [16].

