This study is not without its limitations. First, this study only investigated the short-term efficacy of coach education on player physical activity as the basketball program took place over five consecutive days. Further, by conducting this study as an OYS basketball program (rather than using players’ usual competition teams and coaches) may have limited our generalisability; however, it has increased our internal validity by allowing us to test the efficacy of the intervention in a more tightly controlled environment. The decision to conduct this study in the form of an OYS basketball program (rather than using players’ usual competition teams and coaches) was made to allow us to individually randomise players to different training groups and coaches within their allocated arm each training session period. If this study were conducted in players’ usual competition, sampling would have had to take place on three levels (player, coach, OYS club), each additional level, an additional source of sampling error causing power to drop. By forming an OYS basketball program and individually randomising players to different training groups and coaches, we avoided a clustering effect and thus a cluster randomised controlled trial study design that would require a much larger sample. Studies conducted in a similar setting have observed high intra-class correlations for MVPA (indicating a large clustering effect) [45,54]. Our sample size, then, would have been inflated considerably to reach sufficient power and account for the clustering; which would not have been feasible. Despite this limitation, the present study employed a rigorous study design and used a high-resolution (1-second epochs) objective measurement to assess physical activity. Additionally, this study will provide insight on girls’ motivation, lesson context and leader behaviour (through SOFIT).

The current trial protocol presents, as far as we are aware, the first intervention to be conducted in an OYS context designed to investigate the efficacy of coach education sessions (relative to a no-treatment control) on increasing players’ MVPA and reducing inactivity during training. If the intervention is successful, this study’s findings will support the use of coach education sessions to increase MVPA in OYS; thus, this study’s protocol can be used as a starting point to inform future interventions and strategies to increase MVPA and reduce inactivity during OYS.

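### Rotating players among coaches within an arm does not remove coach clustering from the treatment comparison, so both the claim that it was avoided and the 80% power need correcting

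*Protocol article*

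**What the plan says.** - **Unit of intervention.** Coach education goes to coaches, four per arm (Blinding). They are pair-matched on their groups' mean step count at the two baseline sessions, and one of each pair is randomised to each arm (Randomisation). Each coach plans their own sessions (Study procedure).
- **Rotation.** Players are randomised to arms within site, and then "players were randomised into different training groups and coaches within their allocated arm for each training session period" (Randomisation). The stated purpose is to avoid clustering by coach.
- **Conclusion drawn.** The Discussion says that by this design "we avoided a clustering effect and thus a cluster randomised controlled trial study design that would require a much larger sample". It also reports: "Studies conducted in a similar setting have observed high intra-class correlations for MVPA (indicating a large clustering effect"), and says that allowing for clustering would have enlarged the sample beyond what was feasible.
- **Sample size.** For 80% power at α = 0.05 and d = 0.6, the article concludes that "a minimum sample size of 36 female players for each group was needed" (Sample size and power calculation). It adds 10% for attrition and so arrives at 80. No design effect appears.
- **Analysis.** "Linear mixed models will be used to analyse the differential change between groups on all outcomes from baseline to follow-up", with baseline as covariate (Statistical analysis). No random effects are listed.

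**The concern.** Re-randomising players breaks the permanent link between a player and one coach. It does not expose an intervention player to a control coach. Whatever makes one coach's sessions more active than another's, apart from the education, therefore stays in the difference between arms. Had the article merely left model detail to a fuller document, there would be nothing to raise. Instead it prints a positive claim that clustering was avoided and uses it to justify the sample size.

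At stake is the primary test. A standard error that counts players but not coaches is too small. Residual differences between two sets of four coaches could then be read as an effect of coach education, and the Discussion says that a positive result will support its use. The stated 80% power would also not hold for a test that is valid.

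**Working it through.** **1. The plan's own figure.** Inputs: α = 0.05, power 80%, d = 0.6 and "using a 1:1 allocation ratio" (Trial design). A two-sample t test on independent players gives 36 per group if one-sided (power 0.81). A two-sided test needs 45, and its power at 36 is 0.71. Then 72/0.9 = 80, or 72 × 1.1 = 79.2, rounded up to 80. The article states neither sidedness nor a baseline correlation, which is a separate matter. What counts here is that 36 comes from a calculation with independent players and no coach variance.

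**2. What rotation does to the arm mean.** In any session each of an arm's four coaches takes about a quarter of its players (40 players and 4 coaches per site, so about 10 per coach). However players are shuffled, each coach effect enters the arm mean with weight 1/4. The coach contribution to the variance of an arm mean is thus σ²(coach)/4, with or without rotation.

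**3. Variance of the contrast.** Assumptions: total single-session variance 1; coach effects that persist over both day-5 sessions; a player share of 0.4 of the non-coach variance; 40 players per arm; outcome the mean of the two day-5 sessions.

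Var(difference) = 2 × [ICC/4 + (1 − ICC)(0.4 + 0.6/2)/40]

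At ICC 0.10 this is 2 × [0.025 + 0.01575] = 0.0815, a standard error of 0.285. The coach part, 0.050, exceeds the player part, 0.0315.

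**4. Type I error if players are treated as independent.** Null trials were simulated with 2 sites, 4 coaches and 40 players per site, coaches paired within site on the day-1 group mean, rotation within arm, and a two-sided 5% test adjusted for baseline.

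| Coach ICC (assumed) | Type I error | Multiple of 5% |
|---|---|---|
| 0.02 | 8–9% | 1.6–1.8 |
| 0.05 | 10–14% | 2.0–2.8 |
| 0.10 | 17–19% | 3.4–3.8 |
| 0.20 | 26–28% | 5.2–5.6 |
| 0.30 | 32–34% | 6.4–6.8 |

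At ICC 0 the simulation returned about 5%, as it should. Making the coach effect wholly or partly session-specific moved the results by only one or two points (for example 7% at ICC 0.02 and 15% at 0.10 when wholly session-specific).

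**5. Does rotation help?** With unmatched coaches and persistent effects, the error was 24% without and 25% with rotation at ICC 0.10, and 34% and 38% at 0.20. Rotation makes players within an arm more alike, which shrinks the player-level standard error while the true one keeps its coach term.

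**6. Does matching help?** In part. With rotation and persistent effects, matching lowered the error from 25% to 17% at ICC 0.10 and from 38% to 26% at 0.20.

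**7. Power of a valid coach-level test, d = 0.6 in single-session SD units, two-sided.** Noncentrality is 0.6/√Var. Eight coaches less intercept, arm and site leave 5 df. Four matched pairs leave 3.

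| ICC | Var | Noncentrality | Power, 5 df | Power, 3 df |
|---|---|---|---|---|
| 0.05 | 0.0583 | 2.49 | 52% | 40% |
| 0.10 | 0.0815 | 2.10 | 40% | 31% |
| 0.20 | 0.1280 | 1.68 | 28% | 22% |

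These powers take no credit for matching or baseline adjustment.

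**The case against.** **The model may include a coach term.** The article specifies linear mixed models and lists no random effects, and a condensed article may leave them to a fuller document. This stands: a reader might infer that coach is definitely omitted, and the text does not establish that. Independence of players is an inference from the sample size and from the claim that clustering was avoided. But including a coach term would not rescue the power statement, because the contrast would still have about 5 df, or 3.

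**Coaches were pair-matched.** A reader might infer that the four more active coaches could all fall in one arm by chance. The documents do not support that: one of each matched pair goes to each arm, so on observed day-1 counts the four highest cannot share an arm. Matching on a noisy one-day measure still leaves residual imbalance, as step 6 shows.

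**The ICC is unknown.** A reader might also infer that the error rate is inflated several-fold whatever the ICC. It is not: below about 0.10 the inflation is under threefold. The high values mentioned in the Discussion come from other settings and may not carry over to randomly formed groups with set skill topics and common equipment. The point must stay conditional on the ICC.

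None of these objections makes the claim that clustering was avoided correct for the treatment comparison.

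**Conclusion.** The concern holds in conditional form. The statements that rotation avoided clustering are wrong for the treatment comparison, and the sample size depends on them. If players are analysed as independent, which the article implies but does not state, type I error runs from about 8–9% at a coach ICC of 0.02 to 32–34% at 0.30. Pair-matching lessens the inflation; rotation does not. A valid test of d = 0.6 falls well short of 80% power at every ICC tabulated.

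The figures rest on an assumed ICC range, a player share of 0.4 of the remaining variance, pairing within site and 10 players per coach per session. The power figures also assume coach effects that persist across the two day-5 sessions. The direction follows from the algebra in step 2 for any non-zero coach variance. Because it affects the validity of the primary test, it should be settled before the analysis is run.

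**What to change.** 1. Remove the statements in Randomisation and Discussion that clustering was avoided. Say instead that rotation removes fixed player–coach nesting but leaves the comparison resting on eight coaches. Restate power over a range of coach ICCs.
2. Specify a primary analysis that respects the coach as the unit receiving the intervention. One option is a mixed model on player-by-session MVPA with crossed random effects for player and coach (and coach-by-session if estimable). Adjust it for baseline, session and either site or matched pair, and use small-sample degrees of freedom: about 5 with site, 3 if the pairs are respected.
3. State in advance a fallback to a coach-level, pair-based analysis, because variance components may not be estimable from eight coaches.

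No new data or participants are needed: accelerometry and session times are recorded, and the randomisation assigns each player to a coach for each session. The cost is wider confidence intervals, a lower stated power, and some care in fitting a model with so few coaches.
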